## Abstract

**Background:**

Recently, two nonrandomized, prospective cohort studies used magnetic resonance imaging (MRI) to assess the circumferential resection margin to identify “good prognosis” rectal tumors eligible for primary surgery and have reported favorable outcomes.

**Objective:**

The objective of this project was to conduct a Phase II trial to assess the safety and feasibility of MRI criteria to identify “good prognosis” rectal tumors eligible for primary surgery in the North American setting.

**Methods:**

Patients with newly diagnosed primary rectal cancer attending surgical clinics at participating centers will be invited to participate in the study. The inclusion criteria for the study are: (1) diagnosis of rectal cancer (0-15 cm) from the anal verge on endoscopy and proximal extent of tumor at or below the sacral promontory on computed tomography (CT) or MRI; (2) meets all MRI criteria for “good prognosis” rectal tumor as defined by the study protocol; (3) 18 years or older; and (4) able to provide written consent. The initial assessment will include: (1) clinical and endoscopic examination of the primary tumor; (2) CT chest, abdomen, and pelvis; and (3) pelvic MRI. All potentially eligible cases will be presented at a multidisciplinary cancer conference to assess for eligibility based on the MRI criteria for “good prognosis” tumor which include: (1) predicted circumferential resection margin (CRM) > 1 mm; (2) definite T2, T2/early T3, or definite T3 tumor with < 5 mm of extramural depth of invasion (EMD); (3) any N0, N1, or N2; and (4) absence of extramural venous invasion (EMVI). All patients fulfilling the MRI criteria for “good prognosis” rectal cancer and the inclusion and exclusion criteria will be invited to participate in the study and proceed to primary surgery. The safety of the MRI criteria will be evaluated by assessing the positive CRM rate and is the primary outcome for the study.

**Results:**

We expect to have a minimum of 300 potentially eligible patients, and based on a 30% eligibility rate and 80% participation rate, it is expected that 75 patients will be recruited over the two year study period. A Data Safety Monitoring Committee has been organized, and the study will be stopped if a positive CRM of >10% is reported at any interim assessment, which will occur after every 25 patients accrued in the study.

**Conclusions:**

It is expected that the results of this study will show that use of MRI criteria to identify “good prognosis” rectal cancers eligible for primary surgery will be safe (ie, positive margin less than 10%). Therefore, these results will have significant potential to change the current management of rectal cancer in North America and result in improved quality of life for rectal cancer patients and survivors, while reducing overall health care costs.

**Trial Registration:**

ISRCTN05107772; http://www.controlled-trials.com/ISRCTN05107772/ (Archived by WebCite at http://www.webcitation/6WhhUhXkA).

## Introduction

### Preoperative Chemoradiotherapy for Stage II and III Rectal Cancer

Preoperative chemoradiotherapy (preCRT) is recommended for Stage II and III rectal cancer based on several, well designed randomized controlled trials (RCTs) that have shown preCRT significantly reduces the risk of local recurrence (LR) from 15% to 7.5% at 2 years [1-6]. Unfortunately, while preCRT reduces the risk of LR, it does not improve survival, leads to significantly poorer bowel and sexual function, and increases the risk of developing second malignancies compared to surgery alone [7-11]. Therefore, new approaches to improve selection and limit preCRT to Stage II and Stage III rectal cancer patients who are most likely to benefit from preCRT are important to improve the long term functional results and overall quality of life for rectal cancer patients, provided optimal oncologic outcomes can be obtained.

There are two recent, nonrandomized, prospective cohort studies (United Kingdom, MERCURY, and Germany) that have used magnetic resonance imaging (MRI) to assess the predicted circumferential resection margin (CRM) to identify “good prognosis” rectal tumors eligible for primary surgery [12,13]. The MRI criteria used for each of these studies are shown in Table 1. In these studies, patients with a MRI predicted “good prognosis” tumor underwent primary surgery, and the results showed favorable clinical outcomes with low rates of positive CRMs (3.3%, 4/122; 6.0%, 11/181) and 2 year LR (3.3%, 4/122), respectively.

### Objective of the Study

Therefore, the objective of this study is to conduct a Phase II trial to assess the safety of MRI criteria to identify “good prognosis” Stage II and Stage III tumors eligible for primary surgery in the North American setting.

**Table 1 table1:** MRI criteria for “good prognosis” rectal cancer tumors eligible for primary surgery.

	United Kingdom (Mercury)	German
Predicted CRM	CRM > 1 mm	CRM > 1 mm
T^a^-category and EMD^b^	T1, T2, or T3 with ≤ 5 mm EMD^b^	T1, T2, or any T3
N^c^-category	N0, N1, N2	N0, N1, N2
EMVI^d^	EMVI^d^ negative	Not assessed
Tumor height	Tumors 5 to 15 cm from the anal verge Tumors < 5 cm from anal verge with no invasion of the intersphincteric plane	Tumors 6 to 12 cm from the anal verge

^a^ T=primary tumor

^b^ EMD = extramural depth of invasion

^c^ N=regional lymph nodes

^d^ EMVI = extramural venous invasion

### Study Overview

This is a 2 year Phase II study to evaluate the safety of MRI criteria to identify “good prognosis” Stage II and Stage III rectal cancer eligible for primary surgery. The safety of the MRI criteria will be evaluated by assessing the positive CRM rate in this “good prognosis” subset of the Stage II and Stage III rectal cancer patients. The MRI criteria will be considered safe if a positive CRM rate of less than 10% is achieved.

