## Results

The primary outcome for the study is the positive CRM rate. A positive margin will be defined as any macroscopic or microscopic tumor, discontinuous tumor nodule, or a positive lymph node located within 1 mm of the CRM on final pathologic assessment. We have 30 high volume surgeons at 16 centers participating in this study who see a minimum of 10 new rectal cancer patients over the 18 month time period. Therefore, a minimum of 300 potentially eligible patients will be assessed, and based on the United Kingdom and German studies, it is estimated that 30% (n=90) will be eligible to participate in the study. Assuming an 80% participation rate, it is expected that 75 patients will be recruited over the two year study period.

If seventy-five patients participate, this will provide a 95% confidence interval half-width precision of 6.7% around a point estimate of 10% for the positive CRM rate. If the point estimate for the positive CRM rate is smaller than 10%, the precision around the point estimate will increase.

A Data Safety Monitoring Committee has been organized and will consist of the study statistician, one surgeon, one radiation oncologist, and one pathologist (who are not participating in the study). The study will be stopped if a positive CRM of >10% is reported at any interim assessment, which will occur after every 25 patients accrued in the study.

The secondary outcomes for the study include 2 year LR and disease free survival rates. Descriptive statistics will be used to report: (1) tumor characteristics, (2) positive CRM rate, (3) MRI findings (T-category, N-category, predicted CRM, EMVI), and (4) final pathology (quality of the TME, CRM, T-category, N-category, EMVI). Regression analysis will be performed to assess if any clinical variables are predictive of positive CRM. In addition, comparing the MRI and pathology findings and assessing interobserver agreement for each of the MRI criteria used to identify “good prognosis” tumors will evaluate the accuracy of the MRI interpretation.

This trial is currently recruiting patients.

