This study is highly relevant, as it is expected that the results of this study will show that use of MRI criteria to identify “good prognosis” rectal cancers eligible for primary surgery will be safe (ie, positive margin rate less than 10%). Therefore, these results will have significant potential to change the current management of rectal cancer in Canada and result in improved quality of life for rectal cancer patients and survivors, while reducing overall health care costs. Furthermore, these results would provide the necessary data to determine if an international RCT to address this question would be feasible based on sample size, recruitment, and cost. Last, standardization of preoperative MRI imaging, surgical, and pathological assessment across centers of excellence in Canada will be important for reporting long term outcomes for this study (ie, 2 year survival and LR rates, quality of life), improving the quality of patient care across Canada, and facilitating participation in future clinical trials on both a national and international level.

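### The criteria are called safe on an observed positive CRM rate below 10%, with no confidence limit, and this is then read as a rate that is below 10%

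*Protocol article*

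**What the plan says.** The decision rule is in the Introduction of the Protocol article, under Study Overview: "The MRI criteria will be considered safe if a positive CRM rate of less than 10% is achieved".

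The Results section gives the sample size ("it is expected that 75 patients will be recruited over the two year study period") and justifies it by precision alone: "this will provide a 95% confidence interval half-width precision of 6.7% around a point estimate of 10% for the positive CRM rate". It also sets a stop: "The study will be stopped if a positive CRM of >10% is reported at any interim assessment", with looks "which will occur after every 25 patients accrued in the study".

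The abstract's Conclusions and the last paragraph of the Discussion's Summary state what the study is expected to show. In the Summary the wording is that use of the criteria to identify cancers "eligible for primary surgery will be safe (ie, positive margin rate less than 10" per cent). Both places go on to say that the results could change management.

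For context, the Introduction cites two earlier cohorts with "low rates of positive CRMs (3.3%, 4/122; 6.0%, 11/181").

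**The concern.** The verdict depends on the observed proportion, but the conclusion is about the criteria, that is, about the underlying rate. The confidence interval in Results serves only to justify the sample size and plays no part in the decision. The article's own half-width shows the gap: about 7 percentage points either side of 10% is an interval of roughly 3% to 17%. An estimate just under 10% therefore cannot show that the rate is under 10%.

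Positive CRM is the primary outcome, and a safe verdict is offered as grounds for operating without preoperative chemoradiotherapy. The same Introduction says that this treatment lowers 2-year local recurrence from 15% to 7.5%. Readers of the result need to know what the verdict excludes and how often it would be wrong.

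**Working it through.** **Inputs, all from the Protocol article.** Planned n = 75; safe if the observed rate is below 10%; stop if it exceeds 10% at a look after every 25 patients; earlier cohort rates of 3.3% and 6.0%.

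**1. The article's precision figure.** Wald half-width = 1.96 × √(0.10 × 0.90 / 75) = 1.96 × 0.03464 = 6.79%. The article gives 6.7%, which matches apart from rounding (6.70% corresponds to n = 77).

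**2. The rules as counts.**
- Final: 10% of 75 is 7.5, so safe means X ≤ 7 (7/75 = 9.3%; 8/75 = 10.7%).
- Stop at 25: more than 2.5, so X ≥ 3.
- Stop at 50: more than 5, so X ≥ 6.

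**3. What a safe result excludes.** The exact (Clopper-Pearson) upper limit for x positives solves P(X ≤ x | 75, p) = α, with α = 0.025 for a two-sided 95% interval and 0.05 for a one-sided limit.

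| Result | Observed | Two-sided 95% upper limit | One-sided 95% upper limit |
|---|---|---|---|
| 2/75 | 2.7% | 9.3% | 8.2% |
| 3/75 | 4.0% | 11.2% | 10.01% |
| 7/75 | 9.3% | 18.3% | 16.8% |

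The lower limit for 7/75 is 3.8%. Every safe result from 3/75 to 7/75 has an upper limit above 10% on either version.

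**4. Chance of a safe verdict.** From the final count alone it is P(X₇₅ ≤ 7 | p). With the stops it is P(X₂₅ ≤ 2, X₅₀ ≤ 5, X₇₅ ≤ 7 | p), obtained by exact convolution of three independent binomial blocks of 25.

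| True rate | Final count alone | With stops at 25 and 50 |
|---|---|---|
| 3.3% | 99.7% | 94.9% |
| 6.0% | 92.0% | 77.1% |
| 10% | 52.1% | 36.5% |
| 12% | 30.9% | 20.3% |
| 15% | 10.8% | 6.7% |
| 20% | 1.0% | 0.6% |

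At a true 10%, the stop at 25 ends 46.3% of trials and the stop at 50 a further 8.5%. Another 8.7% reach 75 patients with 8 or more positives (100 − 46.3 − 8.5 − 36.5 = 8.7).

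**5. If a claim of a rate below 10% required the upper limit to be below 10%.** This needs X ≤ 2 of 75. The chance is 1.6% at a true 10%, 55% at 3.3% and 16% at 6.0%. The stops do not alter these figures, because a trial with at most 2 positives in 75 never meets a stop.

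**6. Sensitivity to sample size.** The article's own inputs give 90 × 0.80 = 72 patients. With 72, the final-count figure at a true 10% is 56.7% instead of 52.1%.

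**The case against.** The strongest reply is that this is an estimation study. The sample size rests on precision, no null hypothesis or error rate is claimed, the imprecision is disclosed, and the conclusions are phrased as expectations, with a randomised trial named as a possible next step. A single-arm phase II study designed for precision is legitimate, so the lack of a formal test is not a fault. The article nevertheless goes beyond estimation by attaching the verdict safe to a threshold and equating it with a rate below 10%. Because the article fixes that rule itself, it is not a detail left to an analysis plan.

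A second reply is that the interim stops protect patients. This stands in part. A reader might infer from the final rule alone that criteria with a true rate at or above 10% would often be declared safe. The documents do not support that as a general statement. A study stopped early does not reach the verdict, so the relevant figure at a true 10% is 36.5% and not 52.1%, and it falls to 6.7% at 15% and 0.6% at 20%. The word often fits only the range from 10% to about 12%. The stops are themselves point-estimate rules, however, and they do not change what 7/75 can show.

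A third reply is that the earlier cohorts suggest a true rate of 3.3% to 6.0%, well under the threshold. That may be so, but the study was set up to find out whether the criteria work in North America, so the answer cannot be assumed.

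**Conclusion.** The concern holds with limits. A safe verdict at up to 7 of 75 does not support the statement that the positive margin rate is below 10%. At its edge it excludes only rates above about 17% (one-sided 95% limit 16.8%). With the stops enforced, the rule returns safe in about one trial in three at a true 10%, one in five at 12% and one in fifteen at 15%.

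These figures assume 75 evaluable patients, independent outcomes with a common rate, looks at exactly 25 and 50 with results known before accrual continues, and no safe verdict after a stop. The exact limits treat the 75 as a fixed sample. For the one-sided upper limit at 7/75 this is conservative, since with the stops the chance of a safe verdict at a true 17% is 2.7%, below the nominal 5%.

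A reader might also infer that the 10% threshold is unusable, or that it should be replaced by 2 of 75. Neither follows. As a screen for further study the present rule behaves reasonably, passing 95% of the time at a true 3.3% and 77% at 6.0%. The fault lies in the conclusion drawn from it. This should be fixed, but it does not undermine the design.

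**What to change.** 1. Keep the observed-rate threshold of 10% and describe it as a go/no-go rule for further study.
2. Report the exact (Clopper-Pearson) 95% confidence interval with the positive CRM rate.
3. State that 7 or fewer of 75 excludes only a true rate above about 17% with one-sided 95% confidence.
4. Print the chance of a safe verdict with the stops included: 95% at a true 3.3%, 77% at 6%, 36.5% at 10%, 20.3% at 12% and 6.7% at 15%.
5. In the abstract's Conclusions and at the end of the Discussion, do not equate safe with a rate below 10%. Reserve that claim for an exact two-sided upper limit below 10%, which at 75 patients means 2 or fewer positives.

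The cost is wording and a small table, with no added patients. The downside is a less favourable claim. The stronger claim would be reached only about 55% of the time at a true 3.3% and 16% at 6.0%, so the 2-of-75 bound should govern what is said and not replace the go/no-go rule. If the sponsor wants 80% power to show a rate below 10%, an exact single-stage test at one-sided 5% needs 89 patients (at most 4 positives) if the true rate is 3.3%, or 286 (at most 20) if it is 6.0%.

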## Methods

### Start-Up Period, 0-3 Months

Research Ethics Board approval and data sharing agreements have been obtained at the lead and participating sites for the study. The project will be launched via radiology, surgery, and pathology webinars with all participating physicians (at all sites) to review the study protocol and data collection processes and complete relevant training sets.

### Patient Sample and Recruitment, 3-21 Months

Newly diagnosed rectal cancer patients attending surgical clinics at participating centers will be invited to participate in the study.

The *inclusion criteria* for the study are: (1) diagnosis of rectal cancer (0-15 cm) from the anal verge on endoscopy and proximal extent of tumor at or below the sacral promontory on computed tomography (CT) or MRI; (2) meets all MRI criteria for “good prognosis” rectal tumor as defined by study protocol (see Table 2); (3) 18 years or older; and (4) able to provide written consent.

The *exclusion criteria* for the study are: (1) planned abdomino-perineal resection (APR) based on pretreatment assessment; (2) planned local excision based on pretreatment assessment; (3) T1/early (primary) T2 tumor on preoperative imaging (MRI and/or transrectal ultrasound); (4) suspicious extramesorectal lymph nodes on MRI; (5) unable to undergo MRI due to contraindications (ie, claustrophobia, metal fragments, implanted metal devices); (6) metastatic disease (including extramesorectal lymph nodes, carcinomatosis, liver, lung); (7) pregnancy; (8) inflammatory bowel disease; (9) previous pelvic radiation; and (10) more than one primary tumor.

### Clinical Assessment

A participating surgeon at each center will perform the initial clinical assessment. The surgeon will be responsible for facilitating the standard preoperative assessment that includes: (1) clinical and endoscopic examination of the primary tumor; (2) CT scan of chest, abdomen, and pelvis; and (3) pelvic MRI. The participating surgeon will be responsible for presenting all potentially eligible rectal cancer cases at a multidisciplinary cancer conference (MCC), which must be attended by the surgeon and at least one radiologist and radiation oncologist affiliated with the participating center. Alternatively, if a MCC is not available, the surgeon will be responsible for organizing a multidisciplinary meeting with Radiology and Radiation Oncology Site Leads. At MCC (or multidisciplinary meeting), all patients fulfilling the MRI criteria for “good prognosis” rectal cancer (Table 2) and the inclusion and exclusion criteria will be invited to participate in the study. Figure 1 shows an example of a MRI with a good prognosis tumor. After obtaining consent, this group of patients will proceed to primary surgery.

**Table 2 table2:** MRI criteria for “good prognosis” and “poor prognosis” rectal tumors.

MRI criteria	Good prognosis	Poor prognosis
Predicted CRM	>1 mm (nonthreatened)	≤ 1 mm (threatened)
T-category^a^ and EMD^b^	Definite T2, T2/early T3, or definite T3 with EMD^b^< 5 mm	Definite T3 with EMD^b^ > 5 mm or T4
N^c^-category	Any N0, N1, or N2	Any N0, N1, or N2
EMVI^d^	Absent or equivocal	Present

^a^ Includes, primary tumor, discontinuous tumor nodes, suspicious lymph nodes, and extramural venous invasion; definite T1 and T1/early T2 tumors will be excluded from study protocol

^b^ EMD = extramural depth of invasion

^c^ N=regional lymph nodes

^d^ EMVI = extramural venous invasion

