### Primary Tumor-Category and Extramural Depth of Invasion

The MERCURY trial considered T3 tumors with < 5 mm EMD as “good prognosis” tumors, while the German trial considered any T3 tumor as a “good prognosis” tumor. The rationale for the MERCURY trial definition was based on a population-based study in which T3 tumors were classified based on EMD [22]. This study reported similar LR and disease free survival rates between T2 tumors and T3 tumors with < 5 mm EMD. Based on these data, the MERCURY group conducted a prospective cohort study to assess the accuracy of EMD measured on MRI using the pathologic specimen as the gold standard in 295 rectal cancer specimens. The MERCURY investigators found a mean difference of only -0.05 mm (95% CI -0.49 mm to 0.40 mm) between MRI and pathologic measurements for EMD [14]. Based on this evidence and expert opinion, our group achieved consensus to consider patients with T3 rectal tumors with < 5 mm EMD as having “good prognosis” tumors [23].

While the MERCURY study included T1 tumors as “good prognosis”, the German trial excluded T1 tumors. Since all of the participating centers across Canada currently were not offering preCRT to T1 or T2 tumors, our group decided to exclude definite T1 and T1/early T2 tumors from the study protocol. However, due to the difficulty discriminating T2/early T3 tumors on MRI, our group decided to include T2/early T3 tumors, as we felt there was relatively high potential for these tumors to be understaged on MRI.

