### Summary

Based on these discussions, the following MRI criteria were proposed by the group for “good prognosis” tumors: (1) rectal cancers 0-15 cm from anal verge with proximal extent at or below the sacral promontory on MRI and anterior resection (ie, restorative procedure) is planned; (2) distance to the MRF or predicted CRM > 1 mm (margin not threatened); (3) T2 and T3 tumors with < 5 mm EMD; (4) any N (N0, N1, or N2); and (5) EMVI absent.

A consensus vote on the proposed MRI criteria was conducted. The group voted anonymously using ballots, and the results of the vote were presented to the group. The group discussed the results of the vote, and revisions of the MRI criteria and subsequent rounds of voting were planned as necessary. The investigative team agreed a priori that consensus would be reached if 80% of the group voted “yes” to the proposed MRI criteria and had planned for 2 to 5 rounds of voting. However, after the first round of voting, 91% (31/34) of the participants voted “yes” to the proposed MRI criteria. The results were presented, and the three individuals who voted “no” identified themselves and explained the reasons for their vote. There were two of these individuals that were concerned about the definition of a threatened margin < 1 mm and would have preferred this to be < 5 mm, and the third individual was concerned about including N1 and N2 disease as “good prognosis” tumors. Since consensus had been achieved on the first round of voting, no subsequent rounds of voting were conducted.

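### The objective is limited to Stage II and III, but definite T2N0 (Stage I) patients count in the one positive CRM rate that decides safety

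*Protocol article*

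**What the plan says.** **Objective.** Objective of the Study aims at "Stage II and Stage III tumors eligible for primary surgery in the North American setting". Study Overview says safety is assessed through the positive CRM rate in the good-prognosis "subset of the Stage II and Stage III rectal cancer patients", and calls the criteria safe if that rate is below 10%.

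**Eligibility.** The good-prognosis column of Table 2 (Clinical Assessment) lists "Definite T2, T2/early T3, or definite T3 with" an extramural depth under 5 mm, and accepts N0, N1 or N2. No condition ties T2 to node-positive disease. The Abstract repeats these criteria, and the list put to the vote (Summary) reads "T2 and T3 tumors with < 5 mm EMD". The only T-category exclusion at the low end is "T1/early (primary) T2 tumor on preoperative imaging" (Patient Sample and Recruitment), with definite T1 added in the Table 2 footnote.

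**Analysis.** The Results section makes the positive CRM rate the primary outcome and sets stopping at more than 10% at looks after every 25 patients. Neither is restricted by stage.

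**Rationale.** The T-category section of the Discussion reports that "all of the participating centers across Canada currently were not offering preCRT to T1 or T2 tumors" and uses this to leave out T1 and T1/early T2. For the borderline group it says "due to the difficulty discriminating T2/early T3 tumors on MRI, our group decided to include T2/early T3 tumors". It gives no reason for admitting definite T2.

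**The concern.** Under standard TNM grouping a definite T2N0 tumor is Stage I, so the enrolled population is wider than the one the objective names. By the article's own account of current practice, these patients would not have been offered preCRT, so operating on them first does not test whether it can be withheld.

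The article defines extramural depth as spread beyond the muscularis propria and applies it to T3 and T4. A T2 primary has no such spread, so a lower positive CRM rate is to be expected. If that holds, each T2N0 patient pulls the pooled rate below the Stage II/III rate. The same pooled rate feeds the 10% criterion and the interim rule, so both become easier to pass. The trial could then report safety for a population in which the rate was never separately estimated.

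**Working it through.** **The plan's own figure.** The Results section gives a 95% half-width of 6.7% at a point estimate of 10% with n = 75. The Wald formula gives 1.96 × √(0.10 × 0.90 / 75) = 6.79%. This agrees apart from rounding.

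**Decision limits.** With 75 patients, below 10% means at most 7 positive margins (7/75 = 9.3%; 8/75 = 10.7%). Not exceeding 10% means at most 2/25 and at most 5/50 at the earlier looks.

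**Inputs that the article does not give.** These are the share *f* of definite T2N0 among those enrolled, and their positive CRM rate *p₁*. Both are assumed: *f* from 10% to 40%, *p₁* from 1% to 5%. The nearest published figures in the article are 3.3% (4/122) and 6.0% (11/181), but those are whole good-prognosis cohorts, not T2N0.

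**Formulas.**
- Pooled rate = *f p₁* + (1 − *f*) *p₂*, where *p₂* is the Stage II/III rate.
- Stage II/III rate implied by a pooled 7/75 = (7/75 − *f p₁*) / (1 − *f*). Example: (0.0933 − 0.3 × 0.01) / 0.7 = 12.9%.
- Chance of passing: exact binomial P(X ≤ 7 of 75) at the pooled rate. With the three looks, exact recursion over ≤2/25, ≤5/50 and ≤7/75.

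**Results.** The last three columns take a true Stage II/III rate of 13%.

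| T2N0 share | T2N0 rate | Stage II/III rate implied by 7/75 | Pooled rate | P(≤7/75) | P(pass all three looks) |
|---|---|---|---|---|---|
| 0% | – | 9.3% | 13.0% | 0.23 | 0.14 |
| 10% | 1% | 10.3% | 11.8% | 0.33 | 0.22 |
| 10% | 5% | 9.8% | 12.2% | 0.29 | 0.19 |
| 20% | 1% | 11.4% | 10.6% | 0.45 | 0.31 |
| 20% | 5% | 10.4% | 11.4% | 0.37 | 0.25 |
| 30% | 1% | 12.9% | 9.4% | 0.59 | 0.42 |
| 30% | 5% | 11.2% | 10.6% | 0.45 | 0.31 |
| 40% | 1% | 14.9% | 8.2% | 0.73 | 0.55 |
| 40% | 5% | 12.2% | 9.8% | 0.54 | 0.38 |

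If T2N0 had the same rate as Stage II/III, there would be no dilution at any share.

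**Fair comparator.** The first row assumes 75 Stage II/III patients. Restricting the planned 75 at a 30% share leaves 75 × 0.7 = 52.5. With 52 patients at a true 13%, P(≤5 positive, i.e. below 10%) is 0.32 on the final count. Part of the gap between 0.23 and the pooled figures therefore reflects sample size, not dilution.

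**Precision after restriction.** 1.96 × √(0.09 / 52.5) = 8.1%, against 6.8% at 75.

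**The case against.** The strongest reply is that the intended quantity is the positive CRM rate among all tumors meeting the MRI criteria, and that the Stage II/III wording is loose. The Abstract's objective has no stage limit, the criteria voted on list T2, and the group wanted to validate two earlier cohorts whose criteria, in Table 1, also include T2. This is a legitimate estimand. It does not remove the conflict, because Objective of the Study and Study Overview both name Stage II and III, and the second attaches the safety criterion to them.

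Four further points limit the concern:
- The article gives neither the T2N0 share nor its margin rate, so the size of the dilution is assumption. At a 10% share and a 5% rate, the implied Stage II/III rate is 9.8%, still below the threshold.
- The Discussion calls MRI nodal evaluation relatively poor, and a positive node or discontinuous nodule within 1 mm of the margin counts as positive. Some MRI T2N0 tumors will prove Stage III, and their margin risk need not be close to zero.
- Restricting the primary set has a real price. Keeping 75 Stage II/III patients at a 30% T2N0 share needs 75 / 0.7 ≈ 107 enrolled, against 90 expected to be eligible, and the looks would need new timing.
- MRI and pathologic T- and N-category are reported descriptively, so a later breakdown is possible. That does not alter the rules applied to the pooled rate.

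The article also cites similar local recurrence and disease-free survival for T2 and T3 under 5 mm. Those are different outcomes from margin positivity and do not show that there is no dilution.

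**Conclusion.** The mismatch is explicit in the current text: the objective and safety population are Stage II/III, while the denominator includes Stage I. No reason is given for including definite T2. Dilution toward safe follows if T2N0 tumors have a lower positive CRM rate, which is expected but not documented. Over the assumed ranges, a passing 7/75 implies about 9.8% to 14.9% in Stage II/III. At a true 13%, the chance of passing is 0.29 to 0.73 on the final count (0.19 to 0.55 with the looks), against 0.23 (0.14) for 75 Stage II/III patients and 0.32 on the final count for 52.

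A reader might infer that a passing result would conceal a Stage II/III rate above 10%, or that the primary and interim set must be replaced. The article supports neither. The first depends on two unknown inputs, and the low end of the range stays under 10%. The second is a debatable trade of precision and look timing that leans on uncertain nodal staging. What holds is that a pooled rate alone cannot support a Stage II/III safety conclusion.

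**What to change.** Reconcile Objective of the Study, Study Overview, Table 2, the Results section and the T-category rationale by one of two routes:

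1. Restate the objective and the safety conclusion as applying to all tumors meeting the MRI criteria, including Stage I definite T2N0.
2. Keep the Stage II/III objective and base that safety conclusion on the rate in those patients.

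Under either route:
- Prespecify the positive CRM rate with its confidence interval separately for Stage II/III and for definite T2N0. Classify by MRI stage, with pathologic stage as a check because MRI nodal staging is poor.
- Give both rates to the monitoring committee at each look.
- Draw no Stage II/III safety conclusion from the pooled rate alone.

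T- and N-category are already recorded, so no new data are needed. The cost is a less precise Stage II/III estimate: a half-width of about 8.1% with roughly 52 patients (30% T2N0 share) instead of 6.8% with 75. The first route is the cheaper one, but it narrows what the trial can claim about withholding preCRT.
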